#### **a) Quantitative evaluation**

Information about recruitment plans and targets specified in the trial documentation (protocols/funding application) will be recorded prior to the start of recruitment. This will include:

- The target recruitment figures (ideally for each centre, per month). If a target recruitment line has been provided as a figure (i.e. image), the raw data informing this line should be requested from the TMG or CTU overseeing the study. Where possible, the rationale behind these targets should be explored and recorded.
- The planned period of recruitment

- The planned number of centres

Recruitment data will be regularly collected (e.g. at least monthly) throughout the recruitment period. As a minimum, this will include the number of patients randomised per centre, per month. Ideally, the number of patients screened, eligible, and approached will also be routinely collected per centre, per month.

The timing of interventions stemming from the QRI should be recorded in the form of day/month/year, with a brief description of the activity. All activities should be recorded, including (but not restricted to):

- Feedback of 'phase 1' findings to the CI and/or TMG, including details of the agreed 'plan of action' (and any subsequent plans for intervention).
- 'Global interventions' (not specific to any particular centre – e.g. 'tips and guidance' documents, changes to PILs, early discussion of findings with the chief investigator)
- 'Centre-specific interventions' (e.g. individual or group feedback within a centre).

b) Qualitative evaluation:

Reflective interviews will be conducted with key informants once the collaboration with the QuinteT team is drawing to an end. Key informants will constitute any individuals who have been exposed to QRI interventions or had a role in delivering the QRI. This will likely include the CI, trial manager/coordinator, and recruiters who have received feedback/training.

Interviews will take place face to face or over the phone, and be informed by a flexible topic guide informed by previous work in this area (40). Ideally, interviews will be conducted by an independent member of the QuinteT team who has had no prior direct involvement in the RCT.

#### **7.7.5. Consent processes for the QuinteT Recruitment Intervention**

##### **a) *Health care professional consent***

Recruiting staff and TMG member consent will be obtained through a 'master' consent form that covers all aspects of the QRI. The consent form will set out individual clauses, with the option to select 'Yes' or 'No' for each research activity accordingly. Research staff or the QuinteT researcher will obtain written consent from all staff. This will be a one-off process to cover consent for all future recordings of appointments, interviews, and observations of TMG/investigator meetings throughout the study.

##### **b) *Patient consent***

##### ***Audio recording/observing recruitment appointments:***

Patients will be sent a copy of the QRI information sheet in the post, alongside the main Patient

Information Sheet about the RCT or given both PISs in an initial face to face discussion. Patients will be provided with sufficient time to read the information, ask any questions, and consider their participation in the QRI study.

A two-step consent process will be adopted for audio-recording initial telephone discussions about potential participation in the H4RT study. Research staff will check to make sure the patient has read and understood the QRI information sheet sent in the post, prior to the telephone discussion. Patients will then be asked to provide verbal consent for the telephone discussion to be audio-recorded. Patients who provide verbal consent will subsequently be asked to provide written informed consent for the audio-recording process at their next face-to-face appointment. Future discussions about potential H4RT participation will be audio-recorded subject to receiving this written consent; if patients choose not to provide written consent, the recording made from their initial telephone discussion will be deleted, and no further recordings made. Patients approached face to face will be asked to consent or decline participation in the QRI at the start of the second face to face discussion.

#### ***Interviews:***

Patients will have received information about the interview processes in advance, in the QRI information sheet given or sent in the post. The research staff will reinforce this by explaining the interview process when they discuss the H4RT study processes with patients over the phone and in the face-to-face recruitment appointments. Written consent for the interviews will then be sought during a face-to-face appointment, once the patient has had sufficient time and opportunity to consider their participation in this part of the research. The QRI consent form will include a clause that asks patients if they would be willing to be take part in a future research interview ('Yes' or 'No'). Patients who select 'Yes' may then be approached by the qualitative researcher.

#### **7.7.6. Analysis of QuinteT Recruitment Intervention data**

Full or targeted sections of interviews and audio-recorded appointments will be transcribed verbatim by an approved transcription service/transcriber that has signed the necessary confidentiality agreements with the University of Bristol. All transcripts will be edited to ensure anonymity of respondent. Data will be managed using NVivo software and stored on encrypted drives at the University of Bristol, in line with the university's data storage policies.

Interview data will be analysed thematically using constant comparative approaches derived from Grounded Theory methodology (41). Analysis will be led by the member of the QuinteT team employed to deliver the QRI, with a sample of transcripts from each of set of stakeholder

interviews double coded by a second member of the team. An initial coding frame will be agreed for each set of interviews and reviewed as it evolves through further data collection and analysis. There will an attempt to search for negative cases in relation to themes, and emerging findings will be regularly discussed in team meetings. Evolving descriptive accounts of emerging findings will be prepared throughout the analytical process.

Audio-recorded recruitment consultations and follow up discussions will be subjected to content, thematic, and novel analytical approaches, including targeted conversation analysis (42) and appointment timing (the 'Q-Qat method') (43). There will also be a focus on aspects of information provision that are unclear, disrupted, or potentially detrimental to recruitment and/or adherence. Thematic approaches, and techniques to maintain rigour, will be similar to those described above (for interviews) (43). (43)

Notes from observations of appointments and TMG/investigator meetings will be recorded in a detailed log. Key issues/themes from these notes will be considered alongside emerging findings from interviews and audio-recorded appointments.

Findings from the above sources will be brought together and reported in descriptive accounts and summary reports, and presented to the CI and TMG. The content of these reports will focus on key recruitment issues identified, and potential solutions to address these.

## **7.8 Withdrawal criteria**

The physician responsible for a patient retains the right to advise withdraw of a patient from a trial for appropriate medical reasons, be they individual adverse events or new information gained about a treatment. Participants can withdraw from (a) complying with the allocated trial treatment or (b) providing data to the trial, at any time for any reason without affecting their usual care. In both cases all ethically appropriate efforts will be made to report the reason for withdrawal as thoroughly as possible in a "Withdrawal/ discontinuation" form.

Should a participant wish to withdraw from receiving the allocated trial treatment, efforts will be made to continue to obtain follow-up data, with the permission of the patient or family as appropriate.

## 8 SAFETY

### 8.1 Definitions

| Term                               | Definition                                                                                                                                                                                                                                                                                                                                                                                                                                                                                                                                                                                                                                                                                                                                                                                                                                                   |
|------------------------------------|--------------------------------------------------------------------------------------------------------------------------------------------------------------------------------------------------------------------------------------------------------------------------------------------------------------------------------------------------------------------------------------------------------------------------------------------------------------------------------------------------------------------------------------------------------------------------------------------------------------------------------------------------------------------------------------------------------------------------------------------------------------------------------------------------------------------------------------------------------------|
| Adverse Event (AE)          | Any untoward medical occurrence in a participant to whom a medicinal product has been administered, including occurrences which are not necessarily caused by or related to that product.                                                                                                                                                                                                                                                                                                                                                                                                                                                                                                                                                                                                                                                                    |
| Serious Adverse Event (SAE) | 
A serious adverse event is any untoward medical occurrence that:
 
 
• results in death
 
• is life-threatening
 
• requires inpatient hospitalisation or prolongation of existing hospitalisation
 
• results in persistent or significant disability/incapacity
 
• consists of a congenital anomaly or birth defect
 
 
Other 'important medical events' may also be considered serious if they jeopardise the participant or require an intervention to prevent one of the above consequences.
 
NOTE: The term "life-threatening" in the definition of "serious" refers to an event in which the participant was at risk of death at the time of the event; it does not refer to an event which hypothetically might have caused death if it were more severe.
 |

### 8.2 Safety monitoring

Trial participants will consent to the use of data captured by the UK Renal Registry (UKRR), NHS Digital (NHSD), Information Services Division Scotland (ISD), Patient Episode Database for Wales (PEDW) and Health and Social Care Services Northern Ireland (HSNI) data. The CTU will collect all events associated with hospital admissions from NHSD, ISD, PEDW or HSNI data as appropriate, and deaths from civil registration (NHSD) on a continuous basis. All hospitalisation-requiring and hospitalisation-associated events, and all deaths, will therefore be captured continuously directly by the CTU.

Given (a) the intensive monitoring of dialysis patients in routine clinical care, (b) the comprehensive data on clinical events recorded directly by the CTU, and c) the routine use of both high-volume HDF

and high-flux HD as part of routine NHS care, the H4RT trial will utilise the following risk-adapted safety reporting approach:

1. Adverse events will be regularly screened for:
  - (a) monthly during recruitment and quarterly during follow-up by the local research team and
  - (b) as directed by the DMC using data collected specifically for the trial and data derived from linkage to routine healthcare databases. .
2. Adverse events (AEs) and serious adverse events (SAEs), i.e. adverse events not considered to be directly related to high-volume HDF, do not require to be recorded and reported (using the standard reporting form) to the sponsor by the PI.
3. Adverse reactions (ARs), i.e. adverse events considered to be directly related to high-volume HDF but not serious, also do not require to be recorded and reported (using the standard reporting form) to the sponsor by the PI.
4. Serious adverse reactions (SARs) and suspected unexpected serious adverse reactions (SUSARs), i.e. adverse events considered to be serious and directly related (or possibly/ probably directly related) to high-volume HDF, however, do require reporting (using the standard reporting form) to the CI and the sponsor as described under 8.3 and 8.4 below. The local research team should maintain a log of SAEs that they identify and agree are not SARs. This will not need to be routinely submitted to the CI but will act as a local record of decision making and may be asked for if a site is monitored.
5. Line listings of SAEs and reported SARs & SUSARs will be reviewed monthly by the CI and submitted annually to the DMC and REC.

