### **8.4.2 Chief Investigator**

The chief investigator will be responsible for:

- Review the reported SAEs, SARs and SUSARs monthly, considering the overall safety of participants in the trial and updating the Sponsor, oversight committees and sites as appropriate.
- Using medical judgement in assigning seriousness, causality and expectedness of SAEs, SARs and SUSARs where it has not been possible to obtain local medical assessment.
- Using medical judgement in assigning expectedness.
- Immediate review of all reportable SAEs, SARs and SUSARs.
- Ensuring safety reports are prepared in collaboration with appropriate members of the TMG group for the main REC and DMC.
- Reporting safety information to the independent oversight committees identified for the trial (DMC and TSC).
- Expedited reporting of unexpected SAEs, unexpected SARs and SUSARs to the REC within required timelines.
- Notifying PIs of unexpected SAEs, unexpected SARs and SUSARs that occur within the trial.
- Central data collection of SAEs, SARs and SUSARs.

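### Sections 8.2 and 8.4 give conflicting rules for SAEs, and some serious events without admission or death have no stated route to the CI or DMC

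*Protocol*

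**What the plan says.** Section 8.1 defines an SAE by several criteria. Death and hospitalisation are two of them; life-threatening events and lasting disability also count, and other important medical events "may also be considered serious if they jeopardise the participant or require an intervention to prevent one of the above consequences".

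Section 8.2 sets out a risk-adapted approach that rests partly on central data capture: "All hospitalisation-requiring and hospitalisation-associated events, and all deaths, will therefore be captured continuously directly by the CTU". Its numbered items then say:

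- Item 2: AEs and SAEs not considered directly related to high-volume HDF "do not require to be recorded and reported (using the standard reporting form) to the sponsor by the PI".
- Item 4: "adverse events considered to be serious and directly related (or possibly/ probably directly related) to high-volume HDF, however, do require reporting" to the CI and the sponsor. SAEs that the site agrees are not SARs go into a local log: "This will not need to be routinely submitted to the CI but will act as a local record of decision making". The log "may be asked for if a site is monitored".
- Item 5: "Line listings of SAEs and reported SARs & SUSARs will be reviewed monthly by the CI and submitted annually to the DMC and REC".

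Section 8.3 covers the reporting of unexpected SARs and of SUSARs. Section 8.4.1 makes site staff responsible for getting unexpected SAEs, as well as unexpected SARs and SUSARs, to the Sponsor within 24 hours, with no condition on relatedness or admission. Section 8.4.2 gives the CI monthly review of reported SAEs, expedited reporting of unexpected SAEs to the REC, and "Central data collection of SAEs, SARs and SUSARs".

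**The concern.** The exemption in 8.2 is reasonable only if the central data contain what the sites do not send. The SAE definition is wider than the capture that 8.2 describes. A serious event handled on the dialysis unit without admission can meet the 8.1 definition and leave no trace in hospital statistics or death registration. If the site judges it unrelated to HDF, items 2 and 4 keep it at the site.

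Two things are at stake. First, sites are given instructions that they cannot all obey, so practice will vary between sites. Second, the listing that the DMC receives may be incomplete for events during or around dialysis sessions, which lie close to the treatment being compared. Section 8.4.5 asks the DMC to look for patterns that single cases would not show, and for that it needs these events from both arms. Relatedness is judged by staff who know the allocation (section 7.3), and under 8.2 that judgement is open to outside checking only if a site is monitored.

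**Working it through.** No arithmetic applies. The check is to follow one kind of event, serious but neither fatal nor admitted, through sections 8.1 to 8.4, Table 2 and Appendix 2.

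1. **Judged at least possibly related to HDF, and unexpected.** Reportable to the CI and Sponsor under 8.2 item 4 and 8.3. The route is clear and does not depend on admission.
2. **Judged related to HDF, but expected.** Reportable under 8.2 item 4, which covers all SARs. Outside 8.3, which is limited to unexpected SARs and SUSARs. The two sections disagree on scope.
3. **Judged unrelated, and unexpected.** Site log only under 8.2 items 2 and 4. Reportable to the Sponsor within 24 hours under 8.4.1, and expedited to the REC under 8.4.2. This is a direct contradiction.
4. **Judged unrelated, and expected.** Site log only. Linkage to admissions and deaths does not see it, 8.4.1 does not cover it, and no text carries it into the item 5 listing.
5. **A mandatory-report infection** (MRSA, MSSA, C. difficile or E. coli). Table 2 brings these in from the public health body through the UK Renal Registry, whether or not the patient is admitted. Appendix 2 also makes a blood stream infection believed to be HDF-related a SAR.

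**Does another return fill the gap in case 4?** The site adherence return in section 7.6 records receipt of the allocated modality, attainment of high-volume HDF and water quality testing. It does not record SAEs.

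**What is the source of the item 5 listing?** The protocol does not say. If the SAEs in it come from linkage alone, items 4 and 5 can coexist, but the listing omits case 4 and the central collection in 8.4.2 is not achieved. If they include site-identified SAEs, item 4 contradicts item 5, because the log is not sent. Either way the text needs a change.

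**Are the arms treated alike?** Section 8.2 defines reactions only in relation to high-volume HDF. For a participant receiving high-flux HD as allocated, cases 1 and 2 cannot occur, so a serious non-admitted event falls into case 3, 4 or 5. The same event in the HDF arm may enter case 1 or 2 and be reported. Under 8.2, central reports of non-admitted serious events, apart from linked infections, can therefore come only from patients exposed to HDF. If 8.4.1 prevails, unexpected HD-arm events are recovered but expected ones are not.

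**The case against.** The strongest case on the other side has four parts.

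- **Other routes exist.** A reader might infer that serious events managed on the unit never reach the CI or DMC. The documents do not support that: cases 1 and 5 have routes, 8.4.1 provides one for case 3, and 8.2 item 1(b) lets the DMC direct screening that uses trial-specific as well as linked data. A reader might likewise infer that linkage sees only deaths and admissions. That is true of the capture statement in 8.2 but not of Table 2. This part stands and confines the gap to case 4, plus case 3 if 8.2 prevails.
- **The approach is deliberate.** Section 8.2 gives reasons, including that both treatments are routine NHS care, and 8.4 refers to a Safety Reporting SOP that is not shown. Reduced reporting is a legitimate choice. It does not settle the conflict, because the contradictory instructions all stand in the protocol itself.
- **No size can be given.** It is tempting to multiply the number of dialysis sessions by an assumed event rate. The documents give no rate for serious events without admission, nor the share judged unrelated or expected, so any count or power figure would reflect only the assumption. This part stands in full.
- **Collecting whole logs would be wasteful.** Section 1 gives about 1.5 to 2.0 admissions per patient per year. For 1,550 participants that is 1,550 × 1.5 = 2,325 to 1,550 × 2.0 = 3,100 a year before attrition, nearly all already available through linkage. This stands and argues for sending only the entries that linkage cannot supply.

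**Conclusion.** The point holds as an internal conflict with a narrow reporting gap. Items 2 and 4 of 8.2 cannot be followed together with 8.4.1 and the central collection in 8.4.2, item 5 lacks a stated source for non-admitted SAEs, and 8.2 item 4 and 8.3 differ on which SARs are reportable. SAEs that are not fatal, not admitted, judged unrelated to HDF and, if 8.4.1 prevails, expected have no stated route to the CI or DMC. If 8.2 prevails, unexpected ones share that fate. The HDF-only definition of a reaction also makes central reports of non-admitted events unsuitable for comparison by arm.

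The conclusion rests on the protocol text alone and assumes that the SOP does not override it. The number of events affected is unknown. The primary outcome, built from deaths and admissions, is not touched; the consequence is for safety oversight. The correction is worth making because it is cheap and the DMC listing depends on it.

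**What to change.** - Reconcile 8.2 items 2 and 4 with 8.2 item 5, 8.4.1 and 8.4.2, so that a site has one rule for unexpected SAEs judged unrelated to HDF. Align the SAR scope of 8.2 item 4 with that of 8.3.
- In 8.2 item 4, require sites to send the CTU the log entries for SAEs that did not lead to admission or death, for both arms, giving event, date, seriousness criterion and relatedness. They can go with the adherence return that section 7.6 already schedules monthly during recruitment and three-monthly during follow-up.
- In 8.2 item 5, state that the SAE listing combines these entries with linked admissions and deaths, and that the table by arm goes to the DMC only.

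The log must be kept in any case and the return already exists, so no visits or participants are added. The cost is a protocol wording change and some CTU data entry. Restricting the transfer to SAEs without admission or death avoids matching thousands of admissions against linked records.

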### **8.3 Recording and reporting of unexpected SARs and SUSARs**

All unexpected SARs and all SUSARs occurring from the time of consent until 30 days after the end of the trial must be reported by the PI to the CI and Sponsor within 24 hours of awareness using the SAR/ SUSAR form (see Key Trial Contacts section for emails contact details t). A further review of expectedness will then be undertaken by the CI. The CI will report any reportable SAR and all SUSARs that are related to the research procedures to the Research Ethics Committee and the Sponsor within 24 hours becoming aware of the event. For each reportable SAR and SUSAR the following information will be collected:

- Full details in medical terms and case description;
- Event duration (start and end dates, if applicable);
- Action taken;

- Outcome;
- Seriousness criteria;
- Causality (i.e. relatedness to trial/intervention), in the opinion of the investigator;
- Whether the event would be considered expected or unexpected.

Each reportable SAR and SUSAR must be reported separately and not combined on one SAR/ SUSAR form. Any change of condition or other follow-up information relating to a previously reported SAR/ SUSAR should be documented on the appropriate form (see Key Trial Contacts for email contact details) emailed securely to the CTU and Sponsor as soon as it is available or within at least 15 days of the information becoming available to the research team. Events will be followed up until the event has resolved or a final outcome has been reached.

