### **8.4.1 Principal Investigator/research staff**

Principal investigators (PIs) and research staff at each site will be checking for AEs and ARs when participants attend for treatment /follow-up; they will be responsible for:

- Using medical judgement in assigning seriousness, causality and expectedness. These decisions must involve a medically trained member of the research team and should be recorded on the local log (see 8.2, above).
- Ensuring that all unexpected SAEs, unexpected SARs and SUSARs are documented and reported to the Sponsor within 24 hours of becoming aware of the event and provide further follow-up information as soon as available. Ensuring that unexpected SAEs, unexpected SARs and SUSARs are chased with the Sponsor if a record of receipt is not received within 2 working days of initial reporting.
- Ensuring that all follow up data for reported SAEs, SARs and SUSARs are provided to the CI and sponsor as soon as the event ends or when any new information becomes available.

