#### **9.6 Interim analysis**

A formal interim analysis of all-cause mortality will be conducted using available data and discussed with the DMC. A one-sided  $p$ -value  $< 0.025$  for treatment differences (mortality (HD)  $<$  mortality (HDF)) would be considered a meaningful difference to be explored further. The analysis will take place half-way through the study although the exact timing of the analysis will be set by the DMC who will be guided by recruitment patterns and progress in obtaining permissions for relevant linkages.

|                                                                                                                                                                                                                                                                                                                                                                                             |                                                                                                                                                                                                                                                                                                                                                                                                                                                                                                                                                                              |
|---------------------------------------------------------------------------------------------------------------------------------------------------------------------------------------------------------------------------------------------------------------------------------------------------------------------------------------------------------------------------------------------|------------------------------------------------------------------------------------------------------------------------------------------------------------------------------------------------------------------------------------------------------------------------------------------------------------------------------------------------------------------------------------------------------------------------------------------------------------------------------------------------------------------------------------------------------------------------------|

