**14.2 Appendix 2 – Risk**

Risks associated with trial interventions

- ☐ LOW  $\equiv$  Comparable to the risk of standard medical care
- ☒ MODERATE  $\equiv$  Somewhat higher than the risk of standard medical care
- ☐ HIGH  $\equiv$  Markedly higher than the risk of standard medical care

Justification:

As high-volume HDF involves infusing an additional 20-25L of water back into the patient x3 per week, x52 weeks per year, water quality is crucial to patient safety and has to meet “Sterile dialysate” standards (i.e. bacterial limits  $<10^6$  CFU/mL & endotoxin limits  $<0.03$  EU/mL). Technological developments over the past decade now make it possible to produce such water “on-line”, i.e. continuously in the renal unit, and almost all renal units in the UK are providing on-line HDF as standard care to at least some patients. There remains, however, a small risk of blood stream infection being introduced as part of the HDF process. This risk is mitigated by renal units monitoring water quality on a regular basis. Any blood stream infections that are believed to be related to the HDF will be reported as SARs.

What are the key risks related to therapeutic interventions you plan to monitor in this trial?

How will these risks be minimised?

| Intervention    | Body system/Hazard     | Activity                                | Frequency | Comments                                   |
|-----------------|------------------------|-----------------------------------------|-----------|--------------------------------------------|
| High-volume HDF | Blood stream infection | Water quality monitoring in renal units | Monthly   | As per UK Renal Association Guidelines (6) |
|                 |                        |                                         |           |                                            |
|                 |                        |                                         |           |                                            |

These risks will also be considered by the DMC and incorporated into data updates they request.

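### Sections 8.2, 8.3, 8.4 and Appendix 2 give conflicting reporting rules for expected HDF-related SARs and for unexpected SAEs unrelated to HDF

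*Protocol*

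**What the plan says.** All references are to the protocol.

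- **Section 8.2, item 2.** "Adverse events (AEs) and serious adverse events (SAEs), i.e. adverse events not considered to be directly related to high-volume HDF, do not require" recording on the standard form or reporting to the sponsor by the PI. The item does not ask whether the event was expected.
- **Section 8.2, item 4.** SARs and SUSARs, described there as serious events with a definite, probable or possible direct relation to high-volume HDF, "do require reporting (using the standard reporting form) to the CI and the sponsor as described under 8.3 and 8.4 below". Again there is no test of expectedness. Sites keep a log of SAEs they have decided are not SARs: "This will not need to be routinely submitted to the CI but will act as a local record of decision making".
- **Section 8.2, item 5.** "Line listings of SAEs and reported SARs & SUSARs will be reviewed monthly by the CI and submitted annually to the DMC and REC".
- **Section 8.3.** "All unexpected SARs and all SUSARs occurring from the time of consent until 30 days after the end of the trial must be reported". The time limit is 24 hours from when the site learns of the event, and both the CI and the Sponsor receive the report. The section heading carries the same restriction to unexpected events.
- **Section 8.4.1.** Site staff are responsible for "Ensuring that all unexpected SAEs, unexpected SARs and SUSARs are documented and reported to the Sponsor within 24 hours of becoming aware".
- **Section 8.4.2.** The CI expedites unexpected SAEs, unexpected SARs and SUSARs to the REC, and is also responsible for collecting data on SAEs, SARs and SUSARs centrally.
- **Appendix 2 (14.2).** Bloodstream infection is the only hazard listed for high-volume HDF. "Any blood stream infections that are believed to be related to the HDF will be reported as SARs".

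**The concern.** These are instructions that site staff must act on within 24 hours, and for two kinds of serious event they point in opposite directions. One of those kinds can include the single hazard that the protocol singles out for HDF. If a site reads 8.3 as the operative procedure, which is how 8.2 item 4 presents it, a related bloodstream infection judged expected would not be sent to the CI or sponsor, although Appendix 2 says that any such infection will be reported.

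What would be lost is prompt notice together with the site's medical judgement that HDF was the cause. Hospital and infection data arriving later by linkage do not carry that judgement. Sites that resolve the conflict differently would also report differently, so the SARs that the CI reviews each month would depend partly on which section each site followed.

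**Working it through.** No arithmetic applies. The check is to cross the two attributes that the rules use, relatedness to HDF and expectedness, and to read each section for each resulting class.

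| Class of serious event | 8.2 | 8.3 | 8.4.1 | Appendix 2 |
|---|---|---|---|---|
| Related, unexpected (unexpected SAR / SUSAR) | Report (item 4) | Report | Report | Report, if bloodstream infection |
| Related, expected (expected SAR) | Report (item 4) | Not covered | Not covered | Report, if bloodstream infection |
| Unrelated, unexpected SAE | Exempt (item 2) | Not covered | Report within 24 hours | – |
| Unrelated, expected SAE | Exempt (item 2) | Not covered | Not covered | – |

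The first and last rows are consistent. The second and third are not.

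**Expected SARs.** Item 4 covers them but refers to 8.3 and 8.4 for how to report, and those sections cover only unexpected ones. Adding SUSARs in 8.3 does not fill the gap, because the abbreviation list already defines a SUSAR as unexpected. The CI's further review of expectedness in 8.3 takes place after a report has been received, so it cannot pick up an event that the site judged expected and did not send.

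**Unexpected unrelated SAEs.** Item 2 exempts them. Section 8.4.1 requires them at the Sponsor within 24 hours, and 8.4.2 requires the CI to expedite them to the REC and notify PIs. A site cannot apply item 2 and 8.4.1 to the same event.

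**Recipients.** Item 4 and 8.3 name the CI and the Sponsor for the initial report. Section 8.4.1 names only the Sponsor for the initial report and brings in the CI for follow-up data.

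**SAE line listing.** Item 5 promises a monthly listing to the CI but does not say where its SAE lines come from. The site log is not routinely submitted, so it is not the routine source. Earlier in 8.2 the CTU is said to capture admission-associated events and all deaths continuously by linkage, which is the natural source, but item 5 does not name it or give a start date. Section 9.6 leaves the timing of the interim analysis to the DMC, "who will be guided by recruitment patterns and progress in obtaining permissions for relevant linkages", so a start date is worth stating.

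**The case against.** The strongest defence is that the specific text already governs. Appendix 2 says without qualification that any HDF-related bloodstream infection is reported as a SAR, and 8.2 item 4 agrees. Non-reporting would need a site both to judge the infection expected and to prefer 8.3 over those two passages. The protocol shows no list of expected events, expectedness is a site medical judgement under 8.4.1, and 8.4 refers to a sponsor SOP that is not shown. This stands in part: it is not certain that any infection would go unreported. It does not remove the conflict, because item 4 itself sends the reader to 8.3, and a separate SOP would not make the protocol's own sections agree.

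Several stronger readings are tempting but are not supported.

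- **That SAEs have no central source.** A reader might infer this from the unsubmitted site logs. Section 8.2 names continuous CTU capture by linkage.
- **That linkage is still missing half-way through, leaving years of SAEs only in local logs.** Section 9.6 says only that progress with permissions will guide the timing of the interim analysis. No permission dates are given.
- **That the DMC would not see bloodstream infections.** It can direct screening of trial and linked data (8.2 item 1b), four organisms come through mandatory reporting (Table 2), and Appendix 2 brings the risk into the updates it requests.
- **That SARs on HD are zero by definition and create a false imbalance.** Section 9.1 assumes 15% crossover from HD to HDF, and those patients can have HDF-related SARs. The protocol plans no comparison of SAR counts between arms; its comparative outcomes are mortality, cause-specific admissions and reportable infections.

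**Conclusion.** The contradiction is on the face of the protocol and should be corrected. It affects two of the four classes of serious event: expected SARs, and unexpected SAEs unrelated to HDF. The initial recipient also differs between sections.

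The number of events involved cannot be derived. The documents give no rate of HDF-related bloodstream infection and no list of expected events. It could be zero if every site follows Appendix 2 and item 4, and could include every related infection judged expected if sites follow 8.3.

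The harm falls mainly on prompt reporting to the CI and sponsor with the site's view of causality. It is weaker for the DMC, which has other routes. The primary endpoint and the planned between-arm analyses are not affected. The conclusion rests on the current text of section 8 and Appendix 2 alone.

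**What to change.** Replace the overlapping statements in 8.2, 8.3, 8.4.1, 8.4.2 and Appendix 2 with one rule, best set out as a short table by event class, recipient and time limit, and have each section refer to it. The rule should:

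1. Make HDF-related SARs, including bloodstream infections, reportable whether or not they are judged expected, as 8.2 item 4 and Appendix 2 already state, and amend the heading and text of 8.3 and the wording of 8.4.1 and 8.4.2 to match.
2. Say explicitly whether unexpected SAEs unrelated to HDF are reportable or exempt, with the same answer in every section.
3. Name the same initial recipients throughout.

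In 8.2 item 5, state that the SAE line listing is drawn from the CTU linkage data and from what date.

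Routine submission of the site SAE logs is not asked for. Section 8.2 gives reasons for its risk-adapted approach. At the 1.5 to 2.0 admissions per patient-year quoted in section 1, 1550 participants would generate about 1550 × 1.5 = 2,325 to 1550 × 2.0 = 3,100 admissions a year if all were under follow-up.

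The cost is amendment wording, a note to sites and a few more SAR forms. If unexpected unrelated SAEs are made reportable, there will be further forms, in a number that the documents do not allow to be estimated.
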